#### **2) Participants**

Data will be collected on all participants about other actions that they may be taking to manage their HFNS, including yoga, acupuncture or other behavioural activities (see section 7.4). Collection of such information from each participant will be through questionnaire sent by mail at 6 weeks and 6 months. QoL will be measured by EORTC-QLQ-C30 and will be collected at baseline, 6 weeks and 6 months.

### **5.3.4 Patient Acceptability Assessment**

An evaluation questionnaire will be administered at the end of the 4-week intervention to those participants in the intervention arm.

## **5.4 FOLLOW UP**

All participants will be included in the study from randomisation (time point 0) until 6 months post randomisation (+/- 4 weeks for post intervention data collection: HFNS Rating Scale, HFNS Belief and Behaviour scale, EORTC-QLQ-C30, GAD7, PHQ9, WSAS and PSQI item 6).

All participants will complete their Baseline, 6 week and 6 month questionnaires by paper CRF and will return these via mail to the research team at SCTU (Baseline questionnaires will be posted back to the research team at site), using the freepost envelope provided. All participants will be sent their questionnaires via the post and will be asked to complete and return to the research team at SCTU using the freepost envelope provided. Where questionnaires have not been returned within 10 days of being posted out, participants will be contacted by telephone by a member of the SCTU research team and data may be collected over the telephone.

If requested, one additional questionnaire booklet will be sent out for each time point during the study.

Some of the study questionnaires (NoMAD and the Patient Evaluation Questionnaire) will be sent to the participants via email (using secure nhs.net email or safesend). The forms will be pseudonymised (identified by the participant study ID) and will not contain any personal identifiable information. Participants will complete these questionnaires electronically and then email back their questionnaires using the secure email channel. If requested, patients can be posted out copies to complete at home and return via post to SCTU, using a Freepost envelope.

**NB:** Participants will also have the option of returning a subset of the questionnaires and completing the remaining questionnaires over the telephone with a researcher. Other methods may be implemented in effort to increase the response rate, including sending patients reminder texts or emails, altering the order of presentation of scales; using coloured paper to highlight different sections and scales in the questionnaire booklet.

The opportunity will be taken to implement a study within a trial (SWAT) to explore whether a theory-based cover letter will improve the 6- month paper questionnaire return rate. The full SWAT protocol can be found in appendix 1.

## **5.5 TREATMENT/ASSESSMENT WINDOW**

A window of  $\pm 2$  weeks for the 6 week assessments and  $\pm 4$  weeks for the 6 months assessments for questionnaires, health economics and process evaluation data will be observed.

## **5.6 DEVIATIONS AND SERIOUS BREACHES**

Any trial protocol deviations/violations and breaches of Good Clinical Practice (GCP) occurring at sites should be reported to SCTU and the local Research and Development (R&D) office immediately. SCTU will then advise of and/or undertake any corrective and preventative actions as required. All serious protocol deviations/violations and serious breaches of GCP and/or the trial protocol will immediately be reported to the Health Research Authority (HRA) and Research Ethics Committee (REC).

## **5.7 TRIAL DISCONTINUATION**

In consenting to the study, participants have consented to the trial intervention, follow-up and data collection. Participants may be discontinued from the trial procedures at any time.

### **5.7.1 Reasons for trial discontinuation**

Participants may be discontinued from the trial in the event of clinical decision, as judged by the PI, termination of trial by sponsor and participant choice. Full details of the reason for trial discontinuation should be recorded in the CRF and medical record.

## **5.8 WITHDRAWAL**

The participant is free to withdraw consent from participation in the trial at any time without providing a reason.

Investigators should explain to participants the value of remaining in study follow-up and allowing this data to be used for trial purposes. Where possible, patients who have withdrawn from trial intervention should remain in follow-up as per the trial schedule. If a participant initially consents but subsequently withdraws from the trial, a clear distinction should be made as to what aspect of the trial the participant is withdrawing from. These aspects could be:

1. Withdrawal from trial intervention
2. Withdrawal from further study follow-up
3. Withdrawal from entire study and does not want data to be used.

Details of study discontinuation (date, reason if known) should be recorded in the End of Study paper CRF, completed by the RN (or Trial Manager) depending on which delegate received the request from the patient. If completed by the RN, the form should be emailed to the MANCAN2 Trial Manager (TM). If received by the TM, the TM will complete the End of Study form and notify the PI at site. The RN will notify the patients GP of withdrawal. Any queries relating to potential withdrawal of a participant should be forwarded to the TM immediately via telephone or email.

We will make every effort to reduce loss to follow-up using the methods listed below:

1. We will emphasise the importance of getting follow-up data to all participants at baseline and the different follow-up assessment points.
2. Unless they have explicitly requested otherwise, all participants will be invited to complete follow-up questionnaires.

In addition to the trial, each participant (i.e. staff/patient) has the right to withdraw from the process evaluation at any time and request that any data collected be deleted. It will not be possible for the participant to withdraw their data once the analysis has started because the data collected will already be pseudonymised and have been used. but the participant can inform the research team if they do not want their anonymised interview content to be used in publications.

Participants can withdraw from the process evaluation without giving a reason by contacting the research team.

## 6 SAFETY

### 6.1 DEFINITIONS

**Adverse Event (AE):** any untoward medical occurrence in a participant or clinical trial participant which does not necessarily have a causal relationship with trial treatment or participation. An AE can therefore be any unfavourable and unintended sign (including an abnormal laboratory finding), symptom, or disease temporally associated with the trial intervention or participation (regardless of causality assessments).

**Serious Adverse Event (SAE):** is any untoward medical occurrence or effect that:

- Results in death
- Is life-threatening\*
- Requires hospitalisation\*\*, or prolongation of existing hospitalisation
- Results in persistent or significant disability or incapacity
- Is a congenital anomaly or birth defect
- Other important medical events\*\*\*

\*‘life-threatening’ in the definition of ‘serious’ refers to an event in which the patient was at risk of death at the time of the event; it does not refer to an event which hypothetically might have caused death if it were more severe.

\*\*Hospitalisation is defined as an inpatient admission, regardless of length of stay, even if the hospitalisation is a precautionary measure for continued observation. Hospitalisations for a pre-existing condition, including elective procedures that have not worsened, do not constitute an SAE.

\*\*\*Other important medical events that may not result in death, be life threatening, or require hospitalisation may be considered a serious adverse event/experience when, based upon appropriate medical judgment, they jeopardise the participant and may require medical or surgical intervention to prevent one of the outcomes listed in this definition.

It is the responsibility of the PI or delegate to define an event as ‘not serious’ (AE) or ‘serious’ (SAE). All adverse events that fulfil the criteria definition of ‘serious’, must be reported to SCTU using the SAE report form (see section 6.3.3)

#### 6.1.1 Exceptions:

For the purposes of this trial, the following SAEs **do not** require reporting to SCTU using the Serious Adverse Event Report Form:

- Death due to prostate cancer
- Prostate cancer disease progression
- Hospitalisation for elective treatment of a pre-existing condition

### 6.2 CAUSALITY

A complete assessment of AE causality must always be assessed by the PI or delegate. If any doubt about the causality exists, the local investigator should inform SCTU who will notify the Chief Investigator (CI). Other clinicians may be asked for advice in these cases. In the case of discrepant views on causality between investigator and others, all parties will discuss the case. In the event that no agreement is made, the REC will be informed of both opinions within the required timelines.

**Table 2: Assessment of SAE causality**

| Relationship | Denoted                                       |
|--------------|-----------------------------------------------|
| Related      | Some or clear evidence of causal relationship |
| Unrelated    | No evidence of any causal relationship        |

In terms of event status; **Not related to treatment** would highlight that the SAE is not related to the trial intervention. **Related and unexpected SAE** would be classified as an SAE which is related to the trial treatment/intervention and is unexpected.

## **6.3 REPORTING PROCEDURES**

### **6.3.1 SAE**

At week 6 and month 6, participants will be asked if they have been hospitalised (stayed over night in hospital as an inpatient) during the course of the trial (this does not include planned treatments or hospital visits for an existing medical condition). The SCTU trial management team will notify the relevant PI at site of any indication of hospitalisation that the patient may have reported on their week 6 and month 6 follow-up CRF and will subsequently ask the PI to complete a 'Serious Adverse Event Report Form – Non-CTIMP'.

### **6.3.2 Expectedness**

For the purposes of this trial no SAEs are to be considered expected.

### **6.3.3 Reporting Details**

A 'Serious Adverse Event Report Form – Non-CTIMP' should be completed for all SAEs and emailed to SCTU within 24 hours of the -Principal Investigator becoming aware of the event. The Principal Investigator should complete the SAE form, email a scanned copy of the form with as much detail as possible to the SCTU together with anonymised relevant treatment forms and investigation reports.

Alternatively, SCTU can be contacted by telephone to report the event and then emailed a scanned copy of the SAE report form completed as above as soon as possible.

### **SAE REPORTING CONTACT DETAILS**

*Please email a copy of the SAE form to  
SCTU within 24 hours of becoming aware of the event*

**Email: [[contact]](mailto:[contact])**

**FAO: Quality and Regulatory Team**

***For further assistance: [contact] (Mon to Fri 09:00 – 17:00)***

The responsible investigator (or delegate) should assign the seriousness, causality and expectedness of the event. The event term should be the most appropriate medical term of concept and grades given in accordance with the National Cancer Institute Common Terminology Criteria for Adverse Events version 5 (NCI CTCAE v5). Additional information should be provided as soon as possible if the event has not resolved at the time of reporting.

## 6.4 SCTU RESPONSIBILITIES FOR SAFETY REPORTING TO REC

The SCTU will notify the REC of all **Related and Unexpected** SAEs occurring during the study within 15 days of the report receipt. The SCTU submit all safety information to the REC in an Annual Progress Report.

## 6.5 REPORTING WINDOWS

All SAEs must be reported from the date of consent until end of study. For SAE reporting purposes, end of study is defined as 26 weeks post start date of study intervention/ control (treatment as usual).

See below for SAE reporting windows:

- **Between informed consent and start date of study intervention/ control:** All events that are considered SAEs that are deemed by the investigator to be related to trial procedures
- **From the start date of the study intervention/ control until 26 weeks post start date:** All events are considered to be SAEs

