### **TREATMENT AS USUAL (TAU)**

All patients, regardless of randomised allocation, will receive TAU for HFNS symptoms as determined by their local care team and institutional practice. TAU will be defined as care consistent with NICE guideline NG131, Prostate cancer: diagnosis and management (<https://www.nice.org.uk/guidance/ng131>). This includes access to a specialist prostate cancer urologist or oncologist and a named prostate cancer CNS team member, as well as locally and nationally available cancer information. It also allows for options for pharmacotherapy for HFNS which may include, but are not restricted to, those recommended in NG131.

At the end of the study, all participants that randomise into the TAU arm will receive a copy of the CBT Booklet and CD/ Audio files (demonstrating the breathing and relaxation exercises).

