### 5.3 DATA COLLECTION/ASSESSMENT

The schedule for timing, frequency and method of collection of all trial data is summarised in Table 1. Assessments will be performed as close as possible to the required time point. Ideally the commencement of self-help CBT will begin 3 weeks after randomisation. The duration of the intervention and contemporaneous TAU is 4-weeks. Post-intervention measures will be taken in both groups in parallel (i.e. 6 weeks and 6 months post-randomisation).

The Case Report Forms (CRF) should be completed in black ballpoint pen, with unique participant ID number and initials recorded on the header of each individual form. Information entered incorrectly should only be amended on the original CRF prior to photocopying. Corrections should be made by deleting with a single line through the entry and writing the correct value alongside the box; all amendments should be initialled and dated. Once complete, the CRFs will be photocopied and the copy should be sent to SCTU. The originals should be filed in the appropriate site file folder at the site.

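### The SAE reporting rules in section 6.5 contradict each other and run from a start date that is not defined for the TAU arm, and the question put to men is narrower than the protocol's own SAE definition

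*Protocol*

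**What the plan says.** Section 6.5 (Reporting windows) opens with a general duty: "All SAEs must be reported from the date of consent until end of study". It then sets the end of that period: "For SAE reporting purposes, end of study is defined as 26 weeks post start date of study intervention/ control (treatment as usual". Two bullets follow. For the time between consent and the start date, the reportable set is "All events that are considered SAEs that are deemed by the investigator to be related to trial procedures". For the 26 weeks after the start date, the bullet treats all events as SAEs.

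On timing, section 5.3 says: "Ideally the commencement of self-help CBT will begin 3 weeks after randomisation. The duration of the intervention and contemporaneous TAU is 4-weeks". The same section takes the assessments in both arms at 6 weeks and 6 months after randomisation. Section 5.4 calls randomisation time point 0 and includes men until 6 months after it. Table 1 schedules SAE collection at weeks 6 and 26 only, with windows of 2 and 4 weeks either side.

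On TAU, section 5.2 says: "All patients, regardless of randomised allocation, will receive TAU for HFNS symptoms as determined by their local care team and institutional practice".

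On what is asked at the two follow-up points, section 6.3.1 says: "participants will be asked if they have been hospitalised (stayed over night in hospital as an inpatient) during the course of the trial". Section 6.1 is wider: "Hospitalisation is defined as an inpatient admission, regardless of length of stay, even if the hospitalisation is a precautionary measure for continued observation".

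**The concern.** A reporting window has to tell a site three things: when it opens, when it closes and which events count. Section 6.5 is unclear on all three.

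- **Opening.** The change from related SAEs only to all SAEs hangs on a start date. TAU is continuing local care that both arms receive, so a TAU man has no evident start.
- **Closing.** The end is counted from that same start date, whereas follow-up and the scheduled SAE questions are counted from randomisation.
- **Which events.** The opening sentence and the two bullets cannot all be followed, and the last bullet conflicts with the AE/SAE distinction in 6.1 and the exceptions in 6.1.1.

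In addition, the prompt to men uses a narrower notion of hospitalisation than the definition.

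At stake is the consistency of the safety data. Table 1 schedules SAE collection and no collection of other adverse events, and section 10.3 gives the DMEC's role to the TSC. If sites resolve the text differently, SAE counts may not be comparable between sites, and possibly not between arms.

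**Working it through.** The plan gives no numerical result to reproduce here. The check is date arithmetic plus a comparison of the passages.

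**Inputs**
- Length of full-reporting window: 26 weeks from start (6.5).
- Lag from randomisation to CBT start: 3 weeks, stated as an ideal (5.3).
- Last SAE question: week 26, allowed from 26 − 4 = 22 to 26 + 4 = 30 (Table 1, 5.5).
- TAU start: not defined.

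**Formulas** (weeks after randomisation)
- Window end = lag + 26.
- Gap after the last question = window end − week of that question.

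**CBT arm, lag 3.** Window end = 3 + 26 = 29.
- Question at week 26: 29 − 26 = 3 weeks not asked about, or 3/26 = 11.5% of the window.
- Question at week 22: 29 − 22 = 7 weeks not asked about.
- Question at week 30: 29 − 30 = −1, so the question comes 1 week after the window has closed.

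**TAU arm, two readings**

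| Reading of TAU start | TAU full reporting | CBT full reporting | Difference between arms | Gap after week-26 question, TAU |
|---|---|---|---|---|
| Randomisation | weeks 0–26 | weeks 3–29 | 3 weeks at each end | 0 weeks |
| Same date as CBT | weeks 3–29 | weeks 3–29 | none | 3 weeks |

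An arm difference and a late gap among TAU men therefore cannot both occur at nominal timing. Each belongs to a different reading.

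**Sensitivity to the lag.** Because 3 weeks is only an ideal, lags of 0 to 6 weeks were tried as an assumption. The nominal gap equals the lag: 0 weeks at lag 0, 1 at lag 1, 3 at lag 3 and 6 at lag 6. The same figure is the shift between arms on the first reading. Small lags are not excluded by the text, since Table 1 sets delivery in weeks 1 to 4 on the same scale as weeks 6 and 26.

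**The anchor in the CBT arm.** Section 5.8 lets a man withdraw from the intervention and stay in follow-up. If he does so before the first workshop, he too has no evident start date.

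**Internal consistency of 6.5**
- The opening sentence covers all SAEs from consent. The first bullet limits the period before the start to those related to trial procedures.
- The second bullet, read literally, makes every event an SAE. Section 6.1 separates AEs from SAEs, and 6.1.1 exempts three kinds of SAE from the report form.

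**Question against definition.** Section 6.1 counts an inpatient admission whatever its length. Section 6.3.1 asks about staying overnight. A same-day inpatient admission meets the first and is not prompted by the second. The documents do not say how many such admissions to expect.

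**The case against.** The strongest reply is that safety reporting does not rest on the questionnaire. Section 6.1 requires every serious event to go to SCTU on the SAE form, and 6.3.3 requires the form within 24 hours of the investigator becoming aware. That duty covers same-day admissions and runs to the end of the window. This stands, so a reader who infers that same-day admissions are missed goes too far: they are not asked about. The route still depends on awareness. Follow-up questionnaires go to SCTU and not to the site (5.4), ADT is usually given by a GP nurse (1.1), and no clinical site monitoring is expected (12.2).

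Second, section 5.3 describes TAU as contemporaneous with the intervention, and section 4.5 releases a cohort's allocations at one time, so a shared start date is workable. Moreover, the question in 6.3.1 is the same in both arms, is timed from randomisation and covers the whole course of the trial. SCTU then requests an SAE form whenever an admission is reported. Overnight stays in weeks 0 to 3 are thus prompted for in both arms. This also stands. A reader might infer that capture does differ by arm, but the text supports only that it may.

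Third, the late gap exists at nominal timing only: a month-6 questionnaire completed at week 29 or 30 reaches the end of a week-29 window. This is correct.

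Fourth, the two bullets are evidently meant to specify the opening sentence, and the last one looks like a drafting slip. That is likely, but sites must apply the text as it stands.

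Finally, a reader might take SAE counts by arm to be the trial's only safety comparison. The Protocol does not say so; section 7.3 plans no between-arm SAE analysis, and the SAP is not at hand.

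**Conclusion.** The concern holds as a fault in the current text with limited consequences. Section 6.5 contradicts itself and conflicts with 6.1 and 6.1.1. Its window hangs on a control start date that is never defined, and it uses a different clock from follow-up and the scheduled SAE questions. The question in 6.3.1 is narrower than the definition in 6.1.

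The size depends on the reading. With the 3-week lag, either the arms' full-reporting windows are shifted by about 3 weeks (0–26 against 3–29), or they coincide and the nominal last question falls about 3 weeks before the end, with a range from 7 weeks before to 1 week after. Both figures scale with the lag, which the Protocol gives only as an ideal. A difference between arms is a risk that depends on how sites read the text. Same-day admissions are unsolicited in both arms and rely on the investigator's awareness.

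The primary outcome, sample size and type 1 error rate are untouched. The point merits an amendment because the inconsistency is plain and the remedy is small.

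**What to change.** 1. In 6.5, drop the start-date anchor and define one window for both arms: related SAEs from consent to randomisation, and all SAEs from randomisation to a single stated end point.
2. Reconcile that end point with the 6-month follow-up (5.4), the end of trial (3.4) and the last SAE question (6.3.1, Table 1). A fixed end at week 26 gives the same window in both arms and no nominal gap, but a questionnaire completed at week 22 would leave 4 weeks not asked about. Ending at the 6-month assessment itself closes that gap, but the end date then varies between weeks 22 and 30. Either is workable if stated.
3. Bring the opening sentence of 6.5 into line with the two periods, and replace the last bullet by a rule that all SAEs are reported, subject to 6.1.1.
4. Reword the week-6 and month-6 question to match 6.1: inpatient admission of any length.

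The cost is a short amendment to 6.3.1 and 6.5, one changed CRF question and a few more SAE forms. With a 3-week lag, an end at week 26 after randomisation gives 26 − 3 = 23 weeks of cover after CBT starts, where the present text gives 26. If the full 26 weeks after CBT start are wanted, set a later common end point and schedule an SAE question at it.
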